### Mid-time assessment

After 3 months from the enrollment (Time 1 - T1), each subject will undergo a second clinical and biochemical evaluation in order to obtain a mid-time level of some of the secondary clinical and biochemical outcome measures (Table 1). Only urinary and fecal samples will be collected in order to determine mid-time levels of urinary phthalates and fecal calprotectin.

Anamnestic information about the compliance to the protocol and possible side effects of the treatment will be specifically investigated. Clinical evaluation will include neurological and psychiatric examination along with standardized assessment of GI symptoms, autism severity, sensory-behavioral features, comorbid symptoms, parental stress, and language abilities. Detailed treatment data will be also collected.

### Final assessment

After 6 months (Time 2 - T2) from the enrollment i.e. at the end of the intervention, each subject will undergo a final assessment through the same clinical, biochemical and neurophysiological evaluations performed at T0 in order to establish the after-treatment modifications of all the primary and secondary outcome measures.

### Study design and methodologies

The study will be a double-blind randomized controlled trial with a nutritional supplement and with four parallel arms (see Table 2 for Trial Registration Data). The written informed consent from a parent or legal guardian of children will be obtained by one of the investigators involved in the recruitment, after the study procedures will be explained.

The assessment will be conducted through the administration of the golden standard diagnostic tools for ASD and through the use of psychological testing and scales currently used by scientific community for the definition of core features and comorbid symptoms of ASD. All these evaluations will be performed by a multidisciplinary research team (see Table 3) composed by a pharmaceutical chemical doctor and experienced clinically trained research child psychiatrists and child psychologists, who met standard requirements for research reliability for Autism Diagnostic Observation Schedule-2 (ADOS-2) [61] and Autism Diagnostic Interview-Revised (ADI-R) [62] (which will be described in detail in the Outcome Measures section).

Plasma and urinary levels of inflammatory markers (TNF-α, IL-6, PAI-1), leptin and resistin will be measured by Elisa immunoassay Kits using luminex Technology (Merck Millipore). Concentrations of phthalates and their metabolites will be measured in plasma and urine using LC-MS (Liquid Chromatography–Mass Spectrometry). These measurements will be performed at the molecular laboratory of Institute of Clinical Physiology of National Research Council (Pisa, Italy).

As for the analysis of brain activity and neurophysiological patterns of the recruited subjects, we will use the HCGSN 128 system. All data processing will be run offline on a computer running EEGLAB and a Lab tool for QEEG analysis. The EEG system HCGSN 128 consists of an integrated hardware/software system for recording and analyzing EEG signals from 128 channels. The presence of 128 channels distributed on the surface of the head allows obtaining in a high-density EEG recording with an inter-electrode distance of 35 mm for adults and 10 mm for children. Since the sensor net contains a bigger number of electrodes in comparison with the traditional EEG system, the representation of the distribution of electric potentials on the scalp is much more accurate. The net for the signals recording is constituted by sponges that are immersed in a saline solution to obtain the contact with the skin without abrasion. This characteristic makes the net application faster and less invasive for the subjects and make the system particularly suitable for young children.

### Assignment of interventions

After inclusion in the study and baseline assessment, participants will be assigned to the GI group or to the NGI group depending on their baseline scores at the GI Severity Index [60], as previously described. Then, participants of these two groups will blind receive a treatment with probiotics or with placebo according to a computer generating randomization sequence previously determined by the company supplying probiotic and matched placebo. The allocation ratio of intended numbers of participants will be 1:1 both in the GI and in the NGI comparison groups so that the number of children receiving probiotics or placebo will be identical respectively in the two GI and in the two NGI groups.

Randomization will be made in blocks with random sequences of independent block both in the GI and in the NGI groups; the order of interventions will be vary randomly within each block, so that the assignment blocking schedules will be unpredictable. The study will be double blind till its conclusion, so that subjects, caregivers, all research investigators and all the outcomes assessors will be blinded to treatment group assignment of all subjects till the end of data collection and analysis.

The packages containing probiotics will be indistinguishable from those containing placebo and will be enumerated progressively in the two clinical subgroups (GI: from 1 to 50; NGI from 1 to 50). The allocation sequence will be concealed and the matching between the randomization number and the contents of each package (probiotics or placebo) will be written in sealed envelopes (one for each recruited subject/randomization number) stored at the Institute of Clinical Physiology National Research Council (Pisa, Italy).

The research investigators will assign a number of treatment to each of the recruited children on the basis of their respective progressive order of enrollment inside each of the two subgroups. So, the first child enrolled in the GI subgroup will receive the treatment packages labelled “GI1”, the second child enrolled in the GI subgroup will receive the treatment packages labelled “GI2”, the first child enrolled in the NGI subgroup will receive the treatment packages labelled “NGI1” and so on.

Emergency unblinding will be permissible only in circumstances of harms or serious adverse events. The allocated intervention will be revealed to the parents/legal guardians of the subject by a research collaborator not involved in recruitment, treatment assignment or outcome assessment.

### Outcomes

We aim to evaluate the effects of administration of probiotics in preschooler with ASD with and without GI symptoms through the comparison of several clinical, behavioral and electrophysiological variables in the four subgroups identified. Only at the baseline, the ADI-R [62], a highly-structured interview considered one of the golden standard tool for diagnosis of ASD, will be administered to parents to obtain a standardized symptom profile of each child. Medical history and detailed treatment data will be also collected. As previously described, outcome variables will be assessed at three time points: at the baseline assessment (T0), after an interval of 3 months (T1), and at the end of intervention, after an interval of 6 months from the baseline assessment (T2). All the outcome variables will be assessed in both groups (GI and NGI) and in their respective subgroups in order to determine the effects of probiotics compared with placebo on gastrointestinal symptoms, autistic symptomatology, behavioral, biochemical and neurophysiological patterns (see Table 1).

Moreover, at the baseline, at T1 and at T2, the changes in nutritional status will be evaluated by weight, height and Body Mass Index (BMI) calculation, while the compliance and endurance at probiotic/placebo treatment, the concomitant drug consumption (with particular attention at antibiotic treatment) and the possible adverse events will be monitored by caregivers interview. The treatment compliance and the adverse events will be evaluated also after 15 days from T0 through a call interview. Possible changes in food habits and nutrition will be monitored through the collection and analysis of weekly food diaries that parents/caregivers will fill in during the 6 months of the treatment protocol.

In order to promote participant retention, given the long follow-up of 6 months, appointments will be scheduled in accordance with families’ availability and there will be periodical phone and e-mail contacts of parents/caregivers of patients for monitoring retention. For participants who will be “off-study” after the mid-time assessment (T1), at least a partial mid-time follow-up will be obtained from all the biochemical outcome measures and the clinical outcome measures collected at T1. For participants who will drop out before T1, only the data collected at T0 assessment will be analyzed in order to permit a baseline comparison between the total population of enrolled patients and the subset of patients completing the treatment.

### Primary outcome measure

The primary outcome is the improvement of severity level of ASD symptomatology, measured with ADOS-2 [61] which is a semi-structured assessment of communication, social interactions, play, imagination, and stereotyped or repetitive behaviors for the diagnosis of ASD with a demonstrated inter-rater reliability, test-retest reliability, and internal validity [63]. In this study, the primary outcome measures will be changes in the ADOS Calibrated Severity Scores (ADOS-CSS). The ADOS raw total scores have been already used as outcome measures in previous randomized clinical trials investigating effects of interventions in ASD [64–67]. The ADOS-CSS scores had more uniform distributions across developmental groups, were less influenced by participant demographics than raw totals; therefore, they are useful in comparing assessments across time and identifying trajectories of autism severity for clinical research [68].

### Secondary outcome measures

Clinical outcome measures

The changes in the scores of the following scales and questionnaires will be measured during the treatment in order to evaluate the possible changes in the clinical profiles in children treated with probiotics compared with children treated with placebo (see Table 1).

*The GI Severity Index* [60] is a composite score designed by Schneider and colleagues to capture signs and symptoms of GI distress most commonly reported by parents of children with ASD. The index was constructed by adapting a modified Truelove and Witts Severity Index used for clinical trials in ulcerative colitis [69] to incorporate a total of nine variables relating to GI signs and symptoms: constipation, diarrhea, average stool consistency, stool smell, flatulence, abdominal pain, unexplained daytime irritability, nighttime awakening, and abdominal tenderness. We will collect data about the first eight variables adapting the original items in a self-report questionnaire filled-in by parents of children about the last 3 months. The variable “Abdominal tenderness” will be assessed during the physical exam performed at T0, T1 and T2 by a research physician.

*The Childhood Autism Rating Scale (CARS)* [70] consists of 15 items on socialization, communication, emotional responses, and sensory sensitivities intended to measure the presence and severity of ASD. The child is rated on each item based on the clinician’s observation of the child’s behavior throughout the evaluation as well as on the parent’s report. CARS classifies a child as having mild, moderate, or severe autism, or no autism.

*The Social Communication Questionnaire* (SCQ) [71] is a self-report parent questionnaire with a Current Form which explore ASD specific symptoms in the last 3 months through 40 yes-or-no items.

*The Child Behavior Checklist 1.5-5* (CBCL 1.5-5) [72] is a questionnaire completed by the parents intended to gather information about the child's behavior and which provides scores for seven syndrome scales (Emotionally Reactive, Anxious/Depressed, Somatic Complaints, Withdrawn, Aggressive Behavior, Attention Problems and Sleep Problems), three summary scales (i.e., Internalizing, Externalizing and Total Problems) and five DSM-Oriented scales (Affective Problems, Anxiety Problems, Pervasive Developmental Disorder Problems, Attention Deficit Hyperactivity Disorder Problems, and Oppositional Defiant Problems).

*The Sensory Profile* [73] is a self-report questionnaire which explore sensory processing in children through several items grouped by sensory processing, modulation, and behavioral and emotional responses. The nine factor groupings characterize children by their responsiveness to sensory input including Sensory seeking, Emotional reactive, Low endurance/tone, Oral sensory sensitivity, Inattention/distractibility, Poor registration, Sensory sensitivity, Sedentary, and Fine motor/perceptual.

*The Repetitive Behavior Scale-Revised* (RBS-R) [74] is a questionnaire completed by the parents informing for the presence of a broad spectrum of repetitive behaviors, and recently applied in Italian preschoolers with ASD [75]. It is composed of 43-item scale measuring the breadth of repetitive behavior in children, adolescents, and adults with ASD. It consists of six subscales that have no overlap of item content: Stereotyped Behavior, Self-injurious Behavior, Compulsive Behavior, Routine Behavior, Sameness Behavior, and Restricted Behavior.

*The Parenting Stress Index* (PSI) [76] is a self-report questionnaire designed to evaluate the degree of stress in the parent–child relationship. It yields a Total Score and three domain scores.

The *Vineland Adaptive Behavior Scale II* (VABS-II) [77] is a widely used parent interview scale that assesses adaptive functioning in the areas of communication, daily living, socialization, and motor skills, as well as yielding an adaptive behavior composite score.

Developmental level will be assessed trough *the Griffiths Mental Development Scales-Extended Revised* (GMDS-ER) [78], from which a Developmental Quotient will be obtained.

The MacArthur-Bates Communicative Development Inventories (CDIs) [79] are parent report instruments which capture important information about children's developing abilities in several domains of early language, including vocabulary comprehension, production, gesture use, and early grammar.b)Electrophysiological outcome measures

The modification of the electrophysiological pattern at rest will be evaluated by the comparison of the QEEG features measured at T0 and T2 i.e. power, asymmetry and coherence (a measure of connectivity) computed within each characteristic frequency band of the brain.c)Biochemical outcome measures

In order to value the effects of probiotics compared with placebo on the intestinal and systemic inflammation, LPS, leptin, resistin, TNF-α, IL- 6, PAI–1, phtalates and calprotectin will be measured before and after the treatment (see Table 1).

### Data management and confidentiality

All data will be entered both in paper Case Report Forms (CRF) and in an electronic database immediately after their collection at T0, T1 and T2. In order to protect confidentiality, CRF will be stored inside a locked archive at IRCCS Stella Maris Foundation, while electronic data will be stored in a secured file inside the server of the same institution. Numeric codes from 001 to 100 will be assigned to the recruited subjects on the basis of their respective order of recruitment in the study, and these codes will be reported in the CRF, in the electronic database, in the phials containing biological samples and in the files containing EEG recordings (“P001” for the first recruited child, “P002” for the second recruited child etc.). The matching between the personal data of the recruited subjects and their assigned numeric code will be reported in a separate secured electronic archive, along with their respective randomization code (“GI” from 1 to 50 and “NGI” from 1 to 50, as described above). Research collaborators not involved in outcome assessment will be allowed to access the locked archive and the electronic secured database in order to enter collected data, using unambiguous, standardized terminology and abbreviations to avoid misinterpretation. In order to improve the accuracy of data entry and coding, data entered in the electronic and paper sources will be periodically verified by independent researchers.

The Principal Investigator [name] and the Sub-Investigator [name] and the primary sponsor (IRCCS Stella Maris Foundation) will have access at the end of the study to the full trial dataset, and to the unblinding of treatment assignment. The Italian Ministry of Health can have access to the trial data anytime during or after the trial.

### Statistical analysis, power calculation and sample size

#### Sample size/power

The sample size calculation is based on primary outcome assumption in the intervention and control group. The primary outcome is the improvement of severity level of ASD symptomatology, measured with ADOS-2 which defines the existence of a responder. A recent study carried out by our group gives as an expected rate of responder equal to 62 % [80].

Sample size calculations were performed using the nQuery advisor 6.2 software, based on the primary efficacy variable. Assuming a response rate of 62 % in the placebo group and 90 % in the probiotic group, it was calculated that 38 patients per treatment arm would be sufficient to achieve 90 % power in detecting a treatment difference based on 1-tail w2 test at a significance level of 0.05. Therefore a number of 50 subjects to be enrolled per group was considered sufficient to reach the goal accounting for a certain degree of drop-out rate reported in previous studies on the effects of probiotics [34, 54–56].

In order to achieve adequate participant enrolment to reach target sample size, subjects will be recruited from several clinical settings: 1) Child and Adolescence Mental Health Services of Tuscany Region (Italy), that are first level services for diagnosis and treatment of ASD, dislocated all over the region; 2) The ASD Unit of Child Psychiatry at IRCCS Stella Maris Foundation (Pisa, Italy), a third level institute who receives approximately 250 patients per year (mostly preschool children) for diagnosis from all over Italy; 3) The Unit of Child Rehabilitation at IRCCS Stella Maris Foundation (Pisa, Italy), that is a third level service for treatment of ASD and receives approximately 40 patients per year. At each clinical center involved in the study a child psychiatrist will identified potential subjects, screening them among all their patients through a specific checklist for inclusion and exclusion criteria (Fig. 1). Then the child psychiatrist will informed parents/legal guardians of selected children about the study, giving to them an advertising brochure about the research aims and design and invited them to contact the research team through phone call or e-mail in order to receive further information and to give their agreement to participate. A dedicated phone line will be available at IRCCS Stella Maris Foundation, a research assistant responds during business hours and an answering machine at all other times. All the study visits will be carefully planned and scheduled in accordance with the availability of the families in order to avoid an interference with parents’ work or with the child rehabilitation sections.

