### Objectives (Research aims and hypothesis)

Children with ASD and GI symptoms could represent a distinct ASD endophenotype with specific clinical and neurophysiological features. The exploitation of strategies which can restore normal gut microbiota, and reduce the gut production and absorption of toxins, such as probiotics, may represent a non-pharmacological option in the treatment of GI disturbances in ASD. Moreover, a treatment with probiotics in this subgroup of children with ASD, acting on the gut microflora and on the systemic inflammatory status, could modify their brain activity and function, possibly leading to significant improvement of their behavioral and developmental profiles.

The main aim of this study is to determine the effects of supplementation with a probiotic mixture (Vivomixx®) in ASD children with or without GI symptom. In particular, modifications on ASD core deficits, on cognitive and language development, and on specific GI symptoms will be assessed. The concomitant changes that are associated with administered treatment will be evaluated on a cluster of plasmatic, urinary and fecal biomarkers related to abnormal intestinal function as well as on neurophysiological patterns.

An ancillary aim of the study will be to determine the environmental exposure to phthalates (chemical pollutant) in ASD children, and to evaluate the possible effects of probiotics on their urinary concentrations.

As for the trial design, the study will be a double-blind randomized controlled trial with a nutritional supplement, with four parallel arms, an allocation ratio of 1:1, and a superiority framework.

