#### Data and statistical analysis

All data were will be collected and analyzed independently of the investigators, who will not have access to the data or to its analysis until the latter had been completed. Baseline and demographic data will be tested for balance between treatments using a 1-way analysis of variance (ANOVA), w2 test, or Fisher exact test, as appropriate. As designed by the protocol, the primary comparison for efficacy will be the responder rate according to ADOS 2 score; the analysis will be carried out on the intent-to-treat population, defined as all randomized patients who received at least one dose of study medication. Dropouts will be considered as no responders. Comparison between treatment groups will be carried out by Cochran/Mantel/Haenszel test for responder counts, controlled for basal value, on either the total population of enrolled patients and on the subset of patients completing the treatment. Post hoc-trend analysis of responders within each group will be carried out by the Cochran-Armitage trend test. All data will be analyzed by means of SAS 8.2 Stat Procedures.

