One of the possible outcome of this study is the identification of a subgroup of children with ASD and GI symptoms that could represent a particular endophenotype of ASD characterized by an abnormal gut microflora. We expect that these children, after a probiotic treatment, could show changes in GI symptomatology and in related blood, urinary and fecal biomarkers through their effects in restoring the balance of intestinal microflora, and in attenuating immunological abnormalities [32, 44]. Moreover, we expect that the treatment with probiotics in individuals with ASD and GI symptoms may produce also more significant improvement in autistic symptoms, in behavioral profiles, in adaptive functioning and in cognitive and linguistic development in comparison with individuals with ASD and GI symptoms treated with placebo. As far as we know, this is the first project that aims to examine the impact of this treatment not only on clinical but also on neurophysiological patterns and so it could provide new insights into the gut-brain connection in autism. According to our knowledge, only few studies on the presence of phthalates in subjects with ASD [52, 53] has been conducted. One study of 48 children with ASD and 45 control children reported that urinary concentrations of two phthalates (5-OH-MEHP [mono-(2-ethyl-5-hydroxyhexyl) 1,2-benzenedicarboxylate] and 5-oxo-MEHP [mono-(2-ethyl-5-oxohexyl) 1,2-benzenedicarboxylate]) were significantly increased in the ASD group compared with the control group [52]. Another study reported that 50 children with ASD had decreased glucuronidation of diethylhexyl phthalate, as measured by urinary metabolites, compared with 53 age-matched controls with typical development, despite similar phthalate exposure levels [53]. Notably, glucuronidation is a significant pathway involved in the metabolism of xenobiotics and lower glucuronidation might lead to a decreased detoxification capacity for phthalates. Therefore, the current project could add new data on the relationship between the presence of phthalates, clinical features and neurophysiological patterns in ASD. The expected risks for involved subjects are minimal and related to possible side effects of treatment with probiotics, which, as a dietary supplement, provides mild, transient and not hazardous side effect for the child’s health and to possible side effects related to draw blood that can be considered mild and transient, too. Nevertheless, one of the possible study limitations is the adherence of the families to the whole protocol, since it requires two blood collections, three urinary and fecal collections and two EEG registration and, even if these procedures are not very invasive. During previous analogue researches in our Institute, several families did not accept such kind of procedures for research purposes only. Moreover, adherence of the families could be limited by the blind and randomized study design, given the possibility of not obtaining immediate positive effects for their children if assigned to the placebo groups, mostly due to the relatively long duration of the treatment protocol. Another possible limitation of this study is the lack of a control sample of typically developing children with and without GI symptoms in order to obtain a comparison of the biomarkers levels, the phthalate presence and the neurophysiological findings of ASD subjects. On the basis of the protocol results, if the presence of the hypothesized endophenotype should be confirmed, a subsequent enrollment of a control matched group of children with typical development will be taken into consideration.

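### The 38-per-arm figure and its 90% power hold only for pooled probiotic versus placebo; the text lets them be read as covering the GI and NGI strata, where power is about 76%

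*Protocol article*

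**What the plan says.** **Sizing.** The Sample size/power section sets out a two-group contrast: "Assuming a response rate of 62 % in the placebo group and 90 % in the probiotic group". It continues that "it was calculated that 38 patients per treatment arm would be sufficient to achieve" 90% power on a "1-tail w2 test at a significance level of 0.05", and raises 38 to 50 per group for dropout. It gives no dropout rate.

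**Design.** The Objectives describe a trial "with four parallel arms, an allocation ratio of 1:1, and a superiority framework". Under Interventions the four arms are GI or NGI crossed with probiotic or placebo. Under Assignment of interventions, allocation is 1:1 in blocks within each clinical subgroup, and the packages are "enumerated progressively in the two clinical subgroups (GI: from 1 to 50; NGI from 1 to 50".

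**GI-specific expectation.** The Objectives single out children with GI symptoms as a possible endophenotype whose behaviour may improve. The Outcomes section says that all outcomes will be assessed in both clinical groups and in their subgroups. The Discussion expects that "the treatment with probiotics in individuals with ASD and GI symptoms may produce also more significant improvement in autistic symptoms" than placebo does in children of the same kind.

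**Analysis.** The Data and statistical analysis section compares treatment groups on responder counts by a Cochran-Mantel-Haenszel (CMH) test controlled for the baseline value, with dropouts counted as non-responders. It adds: "Post hoc-trend analysis of responders within each group will be carried out by the Cochran-Armitage trend test". The GI/NGI stratum is not named in either analysis.

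**The concern.** The vocabulary shifts. An arm is one of two in the sample size section and one of four in the Objectives. Fifty per group fits probiotic versus placebo, and it equally fits GI versus NGI, since each of those also has 50. A reader who takes the second meaning will believe that each stratum carries a 90%-powered comparison.

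This matters because the hypothesis that motivates the trial concerns children with GI symptoms. A null result in the GI stratum could pass as a well-powered negative. A significant result in one stratum beside a non-significant one in the other could pass as evidence of an endophenotype-specific effect, although neither analysis described tests that difference.

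**Working it through.** **Inputs.** From Sample size/power: p0 = 0.62 (placebo), p1 = 0.90 (probiotic), so the difference is 0.28; one-sided alpha 0.05; 38 per arm; 50 per group. From Assignment of interventions: 50 GI and 50 NGI, each 1:1, so 25 per arm (derived, not stated).

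**1. Reproduce the plan's figure.** Chi-square without continuity correction, with mean rate 0.76:

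- s0 = √(2 × 0.76 × 0.24) = 0.604
- s1 = √(0.62 × 0.38 + 0.90 × 0.10) = 0.571
- n = [(1.645 × 0.604 + 1.282 × 0.571) / 0.28]² = 37.9, rounded up to 38

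This matches the article.

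**2. Power at other sizes.** Power = Φ[(0.28√n − z·s0) / s1], with z = 1.645 (one-sided) or 1.960 (two-sided):

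| Comparison | n per side | One-sided | Two-sided |
|---|---|---|---|
| Pooled, as enrolled | 50 | 96% | 92% |
| Pooled, as required | 38 | 90% | 83% |
| One stratum, as enrolled | 25 | 76% | 65% |
| One stratum, half of 38 | 19 | 66% (0.655) | 53% |

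For 25 versus 25, one-sided: (1.400 − 0.994) / 0.571 = 0.71, and Φ(0.71) = 0.76. Exact enumeration of the same one-sided chi-square rule gives 78% at 25 and 67% at 19, so the approximation is not the cause of the shortfall.

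**3. Dropouts counted as non-responders.** The article gives no rate, so this is an assumption: the same rate d in both arms, which multiplies both response rates by (1 − d). One-sided power in one stratum at 25 versus 25:

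- d = 10%: 0.558 versus 0.810, power 61%
- d = 20%: 0.496 versus 0.720, power 49%
- d = 24% (the loss implied by 1 − 38/50): 0.471 versus 0.684, power 45%

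**4. Treatment-by-GI interaction.** Assumption: a 28-point effect in GI and none in NGI, with 25 in each cell.

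- SE = √[(0.2356 + 0.0900 + 0.2356 + 0.2356) / 25] = √(0.7968 / 25) = 0.179
- 0.28 / 0.179 = 1.57
- Power = Φ(1.57 − 1.96) = 35% two-sided; Φ(1.57 − 1.645) = 47% one-sided

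**5. What the described analyses can answer.** The CMH test compares probiotic with placebo within levels of baseline value. It gives one overall treatment comparison and, as described, ignores the factor that stratified the randomisation. The trend test is run within each group and its ordering factor is not named. In Table 1, ADOS-2 is scheduled only at baseline and 6 months, so a child has one change and one responder status, with no series over visits. If "group" means treatment group, the test contains no treatment contrast. If it means GI or NGI, it looks at one stratum at a time. On either reading it does not test whether the treatment effect differs by GI status.

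**The case against.** The strongest reply is that the sample size section is coherent on its own terms. It speaks of a placebo group and a probiotic group, and two groups of 50 make the target of 100. The primary comparison is between treatment groups in everyone randomised and dosed, and no sentence confines it to one stratum. This stands. A reader might infer from four arms and 4 × 38 = 152 that the trial falls 52 children short. The documents do not support that: the 38 was calculated for the pooled contrast, which has 96% one-sided power at 50 versus 50 before dropout.

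It is also fair that no power is claimed for a GI-only test. The Discussion sentence is tentative and covers many outcomes, and subgroup contrasts commonly carry no power statement. The point is therefore the unclear scope of the 90%; no stated subgroup power is missed.

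A reader might further treat the absence of an interaction test as an error. An article may leave that to an analysis plan not shown here, and a comparison of probiotic with placebo inside the GI stratum does not strictly need one. Nor can the trend test be called invalid outright: it is labelled post hoc, and its ordering could be baseline severity. What remains is that the responder analyses the article does describe do not bear on the GI question.

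Lastly, the lower figures rest on assumptions that are not in the article: the dropout rates, and an effect confined to GI children. The two-sided figures do not use the planned test. With the plan's own rates and test, the stratum figure is 76%.

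**Conclusion.** This should be fixed, but it is not an arithmetic error in the sample size. The 38 per arm and 90% are correct for pooled probiotic versus placebo. The wording leaves room to attach them to the GI or NGI stratum, where the derived 25 versus 25 gives about 76% one-sided (65% two-sided) at 62% versus 90% with no dropout. If 10 to 20% in each arm drop out and count as failures, this falls to between 61% and 49%. The described CMH test does not name the randomisation stratum, and the within-group trend test cannot address the GI-specific expectation. These conclusions rest on equal strata of 50, as the package numbering implies, and on the article alone.

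**What to change.** 1. In Sample size/power, say that 38, 50 and 90% refer to probiotic versus placebo with GI and NGI pooled. Use one term for the two treatment groups and another for the four design cells.
2. Add GI/NGI as a stratification factor in the primary CMH test.
3. For the GI question, replace the within-group trend test by a pre-specified treatment-by-GI interaction, reported as an estimate with its confidence interval. Acknowledge that its power is low: about 35% two-sided under the scenario in step 4 of the working.
4. Present within-stratum contrasts as estimates, with the stated power of about 76% one-sided before dropout.

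The cost is a change of wording, one extra model term and a less favourable stated power for the subgroups. No extra patients are needed.
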